### Aim

The study will conduct a long-term (7-year) follow-up of the first RCT of a combined Web-based substance use and mental health prevention approach addressing the following research questions:

RQ1: Is the combined approach used in the CSC program more effective in the long-term across the transition into early adulthood (ages 18-21 years) compared with: (1) universal substance use prevention (*Climate Substance Use)*, (2) universal mental health prevention (*Climate Mental Health)*, and (3) education as usual (control condition) for:reducing the use and harmful use of alcohol and cannabisreducing overall symptom levels of anxiety and depressionRQ2: How cost-effective is a combined approach to prevention over the long-term?

We hypothesize that the combined prevention model (CSC program) will be cost-effective compared with (1) school-based prevention as usual, (2) stand-alone universal school-based substance use prevention, and (3) stand-alone anxiety and depression prevention, where Aus $50,000 per quality-adjusted life year is taken as the benchmark for cost-effectiveness in Australia.

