### Measures

Where possible, measures have remained consistent from the original CSC study to the long-term follow-up study. Some measures have been amended or updated to be age appropriate as participants transition out of school. Details of all included measures in the long-term follow-up study are outlined below.

Demographic data including gender, age, country of birth, truancy rates, and academic performance were obtained at baseline to determine the equivalence of groups. All follow-up outcomes will be assessed by validated self-report measures, which have been shown to be valid and reliable in adolescent populations [53-55].

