#### Secondary Measures

##### Social Networks

All participants completing Web versions of the survey will also complete a social networks survey at each time point consisting of questions adapted from O'Malley et al [73] and Lau-Barraco et al [74]. Participants will be asked to nominate up to 6 people with whom they spent most of their free time with in the past 12 months. For each identified person, participants will be asked to report on this person’s demographics, relationships, frequency and mode of contact, perceived mental health symptoms, perceived alcohol consumption, whether they are considered a drinking associate, and relationship closeness. The relationships and closeness between pairs of nominated individuals will also be rated. Although these questions were not included in the original phase of the study, a subsample of participants were asked to nominate their 6 closest friends in their year at school to provide information on their social networks in the original CSC study.

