### Statistical Analysis

Intention-to-treat analyses will be carried out for all primary and secondary outcomes in the trial, including all participants in the groups they were initially randomized to. Multilevel mixed-effects regression models will be used to assess these outcomes. Where appropriate, generalized mixed-effects models will be applied, for example, using logistic regression for dichotomous outcomes.

Multilevel models are able to account for the clustered design of the trial by taking into account the expected correlations between the multiple observations of each participant and between participants in the same school [80]. Multilevel models will include random intercepts for schools and random intercepts and slopes for time for individuals. The best fitting random effects structure for each model will be determined using likelihood ratio tests and model fit statistics such as the Akaike information criterion.

Models will include dummy-coded intervention terms that compare each intervention with the reference control group and time terms reflecting the survey occasion, along with covariates such as gender to adjust for possible confounding. The effects of greatest interest for assessing the effectiveness of the interventions are intervention × time terms that provide baseline-adjusted estimates of how each intervention group has changed relative to control. Interpretable measures of effect size such as odds ratios and standardized mean differences will be calculated for all effects as well their accompanying CIs.

Given that some outcome data are expected to be missing due to loss to follow-up, the analysis must also account for missing data. As mixed-effects models employ maximum likelihood estimation, they produce unbiased estimates when missing data can be assumed to be either missing completely at random or missing at random [81] and are considered to be superior to other strategies for dealing with missing data [82].

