#### Planned Comparisons

The primary aims of the original CSC trial were to assess the efficacy of the combined CSC intervention in comparison with the stand-alone *Climate Substance Use* intervention, *Climate Mental Health* intervention, and standard education received by the control group [83]. Therefore, planned comparisons for each outcome will compare *CSC versus* Control, *CSC versus Climate Mental Health*, and *CSC versus Climate Substance Use* including all participants allocated to each of these intervention groups.

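### The named effectiveness term, intervention × time, has no baseline for the new social-network outcome and is zero there for a constant benefit; elsewhere it answers RQ1 only if wave is categorical, which the article does not say

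*Protocol article*

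**What the plan says.** The Statistical Analysis section sets the scope: "Intention-to-treat analyses will be carried out for all primary and secondary outcomes in the trial". The models contain arm indicators against control, "time terms reflecting the survey occasion", a random school intercept, and a random intercept and time slope per participant. It then names the estimates that matter most for judging effectiveness: "intervention × time terms that provide baseline-adjusted estimates of how each intervention group has changed relative to control".

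Three other places bear on this:

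- **Social Networks (Secondary Measures).** "Although these questions were not included in the original phase of the study", a subsample had named close friends in their school year. The Abstract and the Overall Aim section of the Discussion both list social networks among the secondary outcomes.
- **Measures.** "Some measures have been amended or updated to be age appropriate as participants transition out of school". The instruments concerned are not named.
- **Aim and Sample Size Calculations.** RQ1 asks about effectiveness at ages 18 to 21. The closing power statement is for d=0.15 at the last long-term follow-up. Both describe a difference at particular late waves.

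**The concern.** An interaction with time measures how the gap between arms changes over the occasions in the model. It stands for a treatment effect only when the first of those occasions is a true pre-intervention baseline. If all the data come from years 5 to 7, it measures divergence within those two years, and a benefit established earlier and held moves into the arm main effect, which is not the named estimate.

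Where a baseline exists, the meaning of the term depends on how time enters. With wave as a factor, the interactions at years 5, 6 and 7 are the baseline-adjusted differences that RQ1 needs. With one straight line they are a rate averaged over all years, which need not match the difference at 18 to 21.

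At stake is whether an effect that lasts, or partly lasts, into early adulthood is reported as such. The Introduction says it is unclear whether prevention effects are sustained and asks whether boosters might be needed, so plateau and waning are patterns the study must be able to describe.

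**Working it through.** **The plan's own figure.** The article gives no figure for this term. The nearest is power above 90% for d=0.15 at the final follow-up, with 16 schools × 80 students = 1280 per arm. It cannot be reproduced uniquely, because neither the intraclass correlation (ICC) nor the within-person correlation ρ is given.

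- *Slope interaction*, 7 equally spaced occasions over a unit span, random intercepts only: SE = √[2(1-ρ)/(n·SSx)], SSx = 28/36 = 0.778. With ρ=0, SE = √[2/(1280×0.778)] = 0.0448 and power = Φ(0.15/0.0448 - 1.96) = 91.7%. With ρ=0.5 it is 99.7%.
- *Final-wave difference*: SE = √[2(1+79·ICC)/1280]. Power is 96.7% (ICC 0), 89.5% (0.005), 81.0% (0.01) and 65.6% (0.02).

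The stated figure fits a slope calculation. It fits a final-wave contrast only if the ICC is below about 0.005.

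**No baseline: years 5, 6, 7 only.** Let e be the arm difference (positive = benefit). Mean time is 6 and Σ(t-6)² = 2.

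- Constant e=0.15. Linear: slope = (-1×0.15 + 0×0.15 + 1×0.15)/2 = 0. Categorical: year 6 minus year 5 = 0, and year 7 minus year 5 = 0. The level difference is 0.15 at every wave.
- Fading 0.25, 0.20, 0.15: slope = (-0.25 + 0.15)/2 = -0.05 per year, although the arm is better at every wave.

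This needs no assumed dates or correlations beyond the planned waves.

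**Baseline available, single linear slope (conditional).** The dates of the original-phase surveys are not shown, so assume waves at 0, 0.5, 1, 2, 2.5, 5, 6 and 7 years. With complete data and equal within-person correlation, the generalised least-squares slope equals the ordinary one, Σ(t-t̄)e/Σ(t-t̄)².

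- Time in years: t̄=3, denominator 49.5.
- Time as occasion 0 to 7: t̄=3.5, denominator 42.

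For a step of 0.15 from the first follow-up, years coding gives 0.15×3/49.5×7 = 0.064 and occasion coding gives 0.15×3.5/42×7 = 0.0875. For 0.15 at four school waves then 0.05, they give (0.15×(-6) + 0.05×9)/49.5×7 = -0.064 and (0.15×(-4) + 0.05×7.5)/42×7 = -0.0375.

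| True profile | True change at year 7 | Slope × 7, years | Slope × 7, occasions | Fitted year-7 difference, years |
|---|---|---|---|---|
| 0.15 sustained | 0.15 | 0.064 | 0.0875 | 0.168 |
| 0.15 in school, then 0.05 | 0.05 | -0.064 | -0.0375 | 0.057 |
| Linear growth to 0.15 | 0.15 | 0.150 | 0.159 | 0.150 |
| 0.15 at years 5 to 7 only | 0.15 | 0.191 | 0.1875 | 0.165 |

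The last column is the mean of e plus slope × (7-3); for the first row, 0.131 + 0.00909×4 = 0.168.

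**Sensitivity to dates.** Three other assumed date grids and an occasion index, with and without random slopes, gave the same pattern. A sustained 0.20 was reported as 0.08 to 0.12, and 0.40 falling to 0.15 as -0.17 to -0.08. Linear growth to 0.20 gave 0.20, and a late 0.20 gave 0.24 to 0.26. The fitted year-7 level difference stayed between 0.16 and 0.25 and was never reversed.

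**The case against.** Much of the case on the other side stands.

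- **Linear time is not stated.** The plural terms tied to survey occasion fit wave indicators with baseline as reference at least as well as a straight line. Individual random slopes suggest a numeric time variable, but one can be used in the random part while the fixed part is categorical. The coding may be in an analysis plan that is not shown. A reader might infer that the plan will shrink or reverse real effects; the text does not support that.
- **The slope is not always too small.** It recovers linear growth and overstates late effects, and Sample Size Calculations expects larger effects over the longer follow-up.
- **The missing baseline is documented for one secondary survey**, which the Introduction also treats as a possible moderator or mediator. A reader might suspect the young-adult alcohol consequences scale, a primary measure, but the article says measures were kept consistent where possible and does not name those changed.
- **The model also contains arm terms**, and effect sizes are promised for all effects, so a level difference is estimable. It is still not the estimate named for judging effectiveness.
- **Comparators.** A reader might think that terms defined against control leave out the stand-alone arms. Under Planned Comparisons, "planned comparisons for each outcome will compare" CSC with control and with each stand-alone arm, and linear contrasts of the dummy-coded terms supply these.

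What remains is the no-baseline case. The friend nominations from a subsample of the original phase do not fill the gap: they are a different, narrower set of questions, and not everyone was asked.

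**Conclusion.** The point holds in a limited form and should be fixed.

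*Certain from the text:* for the social-network outcome, the named effectiveness term cannot be baseline-adjusted, and it is exactly zero for any benefit constant over years 5 to 7, however time is coded. The same logic covers any updated instrument without a like-for-like baseline, but which these are, and whether any is primary, is not stated.

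*Conditional:* for outcomes with a baseline, the term answers RQ1 if wave is categorical. If time were a single slope, a sustained 0.15 would be reported as 0.06 to 0.09 and a benefit waning to 0.05 as -0.06 to -0.04. Linear growth would be recovered and late effects inflated. These figures rest on assumed wave dates, complete data and equal within-person correlation.

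A reader might go further and conclude that the RQ1 primary results will be wrong, or that Queensland's earlier survey window calls for a state adjustment. The documents establish neither: no primary instrument is shown to lack a baseline, and no between-arm bias from the timing is shown.

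**What to change.** In the Statistical Analysis section or the analysis plan:

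1. Enter wave as a categorical fixed factor. Individual random slopes on numeric time may stay.
2. Define the RQ1 effect as CSC minus each comparator at years 5 to 7, choosing in advance either the average of the three waves or year 7.
3. Where the same instrument was used at baseline, take this as change from baseline.
4. Where it was not, as for the social-network survey, take the between-arm level difference at those waves and do not call it baseline-adjusted.
5. List which instruments fall under item 3 and which under item 4.

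In every profile examined, wave-specific contrasts return the true effect. The change costs wording and a few more parameters than a single slope, and a wave contrast is less precise if growth really is linear. No extra data are needed.

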#### Planned Comparisons

The primary aims of the original CSC trial were to assess the efficacy of the combined CSC intervention in comparison with the stand-alone *Climate Substance Use* intervention, *Climate Mental Health* intervention, and standard education received by the control group [83]. Therefore, planned comparisons for each outcome will compare *CSC versus* Control, *CSC versus Climate Mental Health*, and *CSC versus Climate Substance Use* including all participants allocated to each of these intervention groups.

#### Economic Evaluation

The cost to deliver each intervention will be combined with the additional resources used by participants over the follow-up period to calculate total costs from the Australian health sector and societal perspectives as recommended by current guidelines [84]. Intervention costs will comprise software development, staff, and teacher time to deliver interventions and usual care. Additional health care resources will be valued by applying standard Australian unit costs (ie, Independent Hospital Pricing Authority, Australian Bureau of Statistics wage rates) to the resource use units collected. The combined CSC intervention group will be compared with the stand-alone intervention groups and the control group in terms of both total costs and outcomes as assessed by an incremental cost-effectiveness ratio. Nonparametric bootstrapping will be used to obtain CIs for cost-effectiveness ratios, as parametric techniques are inappropriate for use on skewed variables and ratios. The sensitivity of the results will be tested against the variation in the utility weights and unit cost prices.

#### Additional Analyses: Moderation of Intervention Effects

To explore possible mechanisms for the interventions’ effectiveness, planned moderation analyses will be conducted to examine whether measures of baseline risk moderate the intervention effects. Baseline measures of risk will be investigated in relation to alcohol and other substance use, harms related to substance use, and mental health symptoms.

## Results

The CSC long-term follow-up study is funded from 2018 to 2022 by the Australian National Health and Medical Research Council (APP1143555). The first follow-up wave commences in August 2018, and the results are expected to be submitted for publication in 2022.

## Discussion

### Overall Aim

This paper outlines the study protocol and design of an extended long-term follow-up of the CSC study cohort into late adolescence and early adulthood. The study aims to (1) examine the long-term effectiveness of a combined universal mental health and substance use program (CSC program) in preventing substance use (and related harms) and reducing mental health symptoms up to 7 years post baseline and (2) evaluate the cost-effectiveness of the program over the long term. In addition, we will explore intervention effects on secondary outcomes including self-efficacy, social networks, peer substance use, emotion regulation, and perfectionism into young adulthood as well as key mediators and moderators of intervention effects.

### Strengths and Limitations

This study will address a significant gap in knowledge by determining for the first time the longevity of school-based universal prevention for substance use and mental health delivered via the Web into young adulthood as well as conducting 1 of the first cost-effectiveness studies of Web-based prevention for mental health and substance use up to 7 years post baseline. Furthermore, this will be the first study to examine unique effects of combining substance use and mental health prevention over the long term. As with the original CSC study, 2 key limitations of the study are participant attrition and reliance on self-report for the majority of measures. Although follow-up rates for the original CSC study remained relatively high across survey waves (ranging from 67% to 88%), it is anticipated that the addition of a new round of consent and participants transitioning from school to postschool environments in this study will present additional challenges and increase study attrition. Anticipated barriers include incomplete and changing contact details, participant relocation (overseas or interstate for travel, study, or work opportunities), and a lack of follow-up support from teachers as participants complete school. To aid in participant follow-up, a set of detailed follow-up strategies will be developed, including a procedure using a wide range of mediums to contact participants (email, SMS, Facebook, phone calls, and mail out), obtaining contact details from one other person who is likely to know how to contact the participant should their contact details change, and adequately reimbursing participants for their time (Aus $20 reimbursement). Reliance on self-report data for the majority of collected measures may introduce bias related to social desirability, particularly in relation to illegal or risky behaviors such as drug use. Nonetheless, self-reported substance use has been shown to be both reliable and valid [53,54], especially when confidentiality is assured and when young people self administer surveys on the Web [55,85], both of which will occur in this study.

### Conclusions

Harms relating to early substance use and development of mental health problems are a serious concern, and the transition into early adulthood represents a key risk period. Despite this, very little is currently known about the effectiveness of school-based prevention programs beyond school age. This study addresses a critical knowledge gap and will indicate if prevention approaches for anxiety, depression, and substance use can have lasting effects. Furthermore, this study will provide a critical economic evaluation of the long-term effects of a combined universal approach to prevent substance use and mental health problems among young people. This knowledge is vital to inform policy both nationally and internationally as economic modeling suggests substantial societal benefit can be gained from even modest reductions in substance use and mental health [48,50,86]. Evidence of sustained benefits into adulthood would provide a scalable and easy-to-implement prevention strategy that could be disseminated immediately, at minimal cost, to reduce the considerable harms, burden of disease, injury, and social costs associated with substance use and mental disorders.

## Appendix

Multimedia Appendix 1 Consort diagram of the Climate Schools Combined study.

Multimedia Appendix 2 Completed Climate Schools Combined (CSC) Study assessments and timeline for extended follow-up assessments.

## Abbreviations

CSC: Climate Schools Combined
DSM-5: Diagnostic and Statistical Manual of Mental Disorders-fifth Edition
NDSHS: National Drug and Alcohol Strategy Household Survey
RCT: randomized controlled trial
SMS: short messaging service
